#### Data collection

Data collection will be at three levels: teacher, principal and youth. Teachers (*N* = 160) and principals (*N* = 40) will complete quantitative assessments on implementation-level outcomes at baseline and post-intervention. All principals and a subset of teachers (*N* = 40) will also complete qualitative exit interviews at post-intervention to explore key aspects of feasibility, acceptability, and adoption, (e.g., usefulness of YRI skill-building exercises), and internal and external factors that might influence facilitator experiences (e.g., school climate, incentives). The subset of teachers will be selected based on a multivariate sampling matrix [31, 32]. We will also explore feasibility and acceptability of mobile-based supervision via key informant interviews with facilitators who received mobile supervision at post-intervention.

Youth (*N* = 1200) will complete quantitative assessments on mental health and daily functioning at baseline and post-intervention. Youth from intervention schools (*N* = 960) will complete quantitative assessments on implementation-level outcomes. A subset of youth (from intervention schools; *N* = 32) randomly selected based on a multivariate sampling matrix will complete exit interviews at post-intervention to obtain their feedback on YRI feasibility, acceptability, and barriers/facilitators to adoption. We will also collect data on educational outcomes for all youth via administrative records (i.e., school attendance, grades, tardiness, disciplinary reports) at baseline, post-intervention and 12-month follow-up. All youth will complete the EQ-5D-3 L at baseline, post-intervention and 12-month follow-up to inform the cost-effectiveness analysis [33].

Trained RAs will administer assessments electronically via tablets. All classroom instruction, assignments and tests are completed in English in our catchment area, thus the Western region schools, assessments and interviews will be completed in English as a first option. Versions of all study assessments will also be available in Krio (the local language) for any participants indicating difficulties with English fluency or a preference for completing assessments in Krio. All measures have been forward and backward translated from English to Krio previously. We will report data disaggregated by sex.

### Measures

#### Implementation outcomes

Feasibility, acceptability, appropriateness, adoption, sustainment, and organizational climate will be assessed via the Implementation Science Questionnaire developed at Johns Hopkins Bloomberg School of Public Health [34]. We have used these measures in prior research in Sierra Leone [20, 21], and the scales demonstrated strong psychometric properties (α = 0.79 − 0.90). The measures will be administered to youth, teachers and principals at baseline and post-intervention. Readiness for Implementing Change will assess readiness to change [35]. This measure has been used cross-culturally and has demonstrated strong psychometric properties (α = 0.94). These core constructs will also be probed via post-intervention key informant interviews with youth, teachers, and principals. We will administer the System Usability scale at post-intervention to assess mHealth app usability [36]. Fidelity will be assessed using the YRI fidelity checklists completed either via an electronic fillable form in the app (mobile supervision condition) or using Excel spreadsheets (standard supervision).

#### Youth mental health outcomes

The Difficulties in Emotion Regulation Scale (DERS), will assess emotion regulation skills [37]. The DERS is a 36-item scale scored on a 5-point Likert scale, with higher scores reflecting greater difficulties regulating emotions (α = 0.91). The Hopkins Symptom Checklist (HSCL) will measure symptoms of anxiety and depression [38, 39]. The HSCL-25 consists of ten items scored on a 4-point Likert scale for anxiety symptoms (α = 0.82) and 15 for depression symptoms (α = 0.82), with higher scores reflecting worse functioning. The Adapted Youth Risk Behavior Survey is a 14-item scale adapted from the original 89-item scale that will assess priority health risk behaviors among youth (i.e., behaviors that contribute to unintentional injuries and violence, tobacco use, alcohol and other drug use, sexual behaviors that contribute to unintentional pregnancy and sexually transmitted infections) [40, 41]. Items include both binary (yes/no) and multiple response options. The World Health Organization Disability Assessment Schedule (WHO-DAS)-2.0 short form will assess functional impairment [42]. The WHO-DAS short form consists of 12-items measuring functional impairment across 5 domains: mobility, self-care, understanding and communication, life activities and societal participation. Items are scored on a 5-point Likert scale and summed to derive a total scale. Higher scores indicate worse functioning [40]. The EuroQual-5 Dimension (EQ-5D-3 L) will be used to calculate quality adjusted life years (QALYs) among youth for the cost-effectiveness analysis [43]. The EQ-5D-3 L is designed for describing and valuing health in terms of 5 dimensions: mobility, self-care, usual activities, pain/discomfort, and anxiety/depression [33]. Each dimension has 3 response categories rated as “no problems”, “some problems”, or “extreme problems”.

### Data analysis

#### Quantitative analysis

We will compare fidelity trajectories of teachers receiving mobile supervision to those of teachers receiving standard supervision and investigate the null hypothesis that mobile supervision will not differ from standard supervision. We will conduct exploratory analyses to uncover typical trajectories for each supervision method (mobile-based or standard) and undertake comparisons using growth curve modeling by means of multilevel models [44]. We will use HLM software (v.8.2), which estimates multiple imputations based on the dependencies of multilevel data. Missing time points are addressed by the multilevel approach to growth modeling, and data from all enrolled participants can be analyzed in accordance with our intention to treat design. The null hypothesis is that the outcomes for the mobile supervision YRI groups will not differ from those in standard supervision YRI groups. With this approach, we can compare both YRI models (as identified by dummy variables) to the untreated control group or assess the null hypothesis of no difference between the fidelity in the two models (mobile-based vs. standard supervision).

We will also investigate the null hypothesis that mobile supervision will not differ from standard supervision at post-intervention in youth outcomes. To investigate YRI effects on mental health among youth at post-intervention, we will use multilevel models to accommodate the clustering of students within YRI groups. For analysis of student outcomes, student characteristics will be modeled in a level-one equation. The group characteristics will be modeled in the level-two equation. School characteristics will be incorporated into a third level.

However, we do not expect a significant school-level intraclass correlation (ICC) for targeted YRI outcomes. In the event we do not find a significant ICC, sector and rural/urban will be represented in the group-level equation, and a two-level model will be estimated.

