### Study aims

This study will implement the evidence-based YRI as an extracurricular resilience-building activity for youth in Sierra Leone’s secondary schools and train teachers to deliver the intervention. Teachers will receive either mobile phone-based supervision or standard in-person supervision to deliver the YRI. Mobile-based supervision will integrate WhatsApp with an mHealth app designed to support fidelity monitoring and feedback during supervision. Study aims are to: (a) examine the feasibility, acceptability, cost, and fidelity to the YRI delivered by teachers receiving mobile-based supervision compared with those receiving standard supervision; (b) compare the effectiveness of the YRI delivered in schools by teachers who receive either mobile-based supervision or standard supervision; (c) investigate potential mechanisms of YRI adoption and sustainment within schools, including readiness to change and organizational climate; (d) conduct a cost-effectiveness analysis to evaluate the relative costs vs. benefits of the YRI delivered in secondary schools with mobile-based supervision and standard supervision from a broad societal perspective, including educational outcomes.

We hypothesize that: (a) mobile-based supervision will be more feasible, acceptable, and cost-effective than standard supervision, and YRI fidelity scores for mobile supervision will be comparable to standard supervision; (b) youth mental health, emotion regulation, and daily functioning outcomes in mobile supervision will not differ from those in standard supervision over time; (c) readiness to change, organizational climate, and teacher buy-in will moderate YRI adoption and sustainment; (d) the YRI incremental cost-effectiveness ratio in both conditions will surpass the standard willingness to pay threshold [16].

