### Study design

We will conduct a hybrid type 3 implementation-effectiveness cluster-randomized trial design [25] to investigate mobile-based supervision of YRI delivery by teachers in Sierra Leone’s secondary schools as a new implementation strategy, with clinical outcomes of the YRI on youth mental and behavioral health as secondary outcomes. We will use a mixed methods approach to investigate study aims. The Exploration, Preparation, Implementation, Sustainment (EPIS) framework [26], a broad, context sensitive implementation science process model, will guide study implementation. Randomization to study condition will occur at the level of the school. Schools (*n* = 50) will be randomized to YRI with mobile-based supervision (*n* = 20 schools/*n* = 480 youth), YRI with standard (in-person) supervision (*n* = 20 schools/*n* = 480 youth) or control (*n* = 10 schools/*n* = 240 youth). Control schools are necessary primarily for the cost-effectiveness analysis because they will provide reference level estimates of QALYs gained by intervention schools. We selected an unequal randomization design to reduce the number of youths who are exposed to the waitlist control [27]. We will offer YRI training to interested teachers in control schools following 12-month follow-up data collection. To optimize comparability between schools, we will match schools into quintets using an algorithm prior to randomly assigning two members of each quintet to each supervision model and the fifth to the control. All research assistants and data analysts will be blinded to participant assignment and will assign schools to study condition based on the allocation sequence.

Regarding standard reporting, this study will adhere to the Standard Protocol Items: Recommendations for Intervention Trials (SPIRIT) guidelines (See Fig. 2) and the Consolidated Standards of Reporting Trials (CONSORT). This trial is registered with the Clinical Trials Registry maintained by the National Library of Medicine at the National Institute of Health (Trial ID: NCT05737667; registered on 02/02/23). This study is approved by the Brown University Institutional Review Board (Protocol #2,022,003,442) and the Sierra Leone Ethics and Scientific Review Committee. Any subsequent modifications will be reviewed by both of these review committees for approval and then submitted to the Clinical Trials Registry as an amendment. The study protocol was also eviewed as part of the funding application.

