#### Statistical power analysis for fidelity to YRI implementation

To assess the minimal detectable effect size for the two-tailed null hypothesis of no difference for fidelity of groups receiving mobile versus standard supervision requires an estimate of the within-group ICC for fidelity for which there is no clear guidance in the literature. Given our standard assumptions, at a small to medium ICC of 0.2 for a two-tailed test with a null hypothesis of no difference for 80 groups and 12 fidelity ratings, the minimum detectable effect size would be 0.30, while at a large ICC of 0.5 the minimum detectable effect size would be 0.41.

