#### Statistical power analysis for student outcomes

Power will be sufficient to assess our secondary aim and examine the hypothesis that the YRI delivered by teachers participating in mobile supervision will be noninferior in terms of youth mental health outcomes compared to the YRI delivered by teachers receiving standard supervision. At a power of 0.8 and an alpha of *p* <.05 (one-tailed to assess noninferiority), using an ICC of 0.03 (based on prior ICCs for mental health outcomes of 0.01-0.04) [18] for the group for comparisons at a single time point (post-intervention or 12-month follow-up) for student outcomes, the minimal detectable standardized effect size for a standardized difference (d) between the two of 0.21; in other words, at a negative difference of 0.21 or smaller, mobile supervision will be considered noninferior to standard. To test individual null hypotheses that either YRI implementation model (20 schools per YRI supervision mode) is superior (one-tailed) to the 10 untreated control schools with regard to mental health or educational outcomes, we have 0.8 power to detect a standardized effect of 0.26. In a comparison of all 40 YRI schools as compared to the 10 control schools, the minimum detectable effect would be 0.21.

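### Fidelity is hypothesised to be comparable, but the stated two-tailed test of no difference cannot support that claim; for youth outcomes the article states two conflicting tests

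*Protocol article*

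**What the plan says.** **Fidelity.** The Study aims section of the protocol article hypothesises that "YRI fidelity scores for mobile supervision will be comparable to standard supervision". The Quantitative analysis section plans to compare fidelity trajectories under mobile supervision "to those of teachers receiving standard supervision and investigate the null hypothesis that mobile supervision will not differ from standard supervision", using growth curves fitted as multilevel models. The power section for fidelity then gives minimum detectable effects for the "two-tailed null hypothesis of no difference for fidelity of groups receiving mobile versus standard supervision", "for 80 groups and 12 fidelity ratings": 0.30 at an ICC of 0.2 and 0.41 at an ICC of 0.5. Alpha and power are not given there beyond a reference to standard assumptions. The article gives no margin for fidelity.

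**Youth outcomes.** The Quantitative analysis section says: "We will also investigate the null hypothesis that mobile supervision will not differ from standard supervision at post-intervention in youth outcomes". The power section for student outcomes instead sets out the hypothesis that YRI delivered under mobile supervision "will be noninferior in terms of youth mental health outcomes compared to the YRI delivered by teachers receiving standard supervision". It uses a one-tailed alpha of 0.05, power of 0.8 and a limit of 0.21 SD. The Study design section places these outcomes second: "with clinical outcomes of the YRI on youth mental and behavioral health as secondary outcomes".

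**The concern.** In a test of no difference, the data can only count against the null. Here the null is what the investigators hope to show. A significant result in either direction rejects it, so failure to reject is the only outcome that agrees with the hypothesis of comparable fidelity. But failure to reject can arise from a true difference near zero, or from a real deficit estimated too imprecisely to detect. The noisier the fidelity ratings, the more likely it becomes. Conversely, a small deficit that the sponsor would tolerate could reject the null if it were estimated precisely.

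This bears on the trial's main argument. The article presents mobile supervision as a route to scaling out the programme and expects it to be more feasible, acceptable and cost-effective. Comparable fidelity is the safeguard on that argument, and fidelity is the only implementation outcome with its own power calculation in the article.

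For youth outcomes the two sections give opposite readings of an imprecise result. A wide interval that covers both zero and a deficit beyond 0.21 SD would leave the null of no difference standing, yet would fail the noninferiority test.

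**Working it through.** **Inputs.** From the fidelity power section: 80 groups, 12 ratings per group, ICC 0.2 or 0.5, two-tailed. Assumed: 40 groups per arm (two groups in each of 20 schools), alpha 0.05, power 80% (as stated for youth outcomes), total rating variance scaled to 1, the contrast taken as the mean over the 12 ratings, and no school-level clustering or gain from matching.

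**Standard error of the arm difference.** SE = sqrt(2 × (ICC/40 + (1 − ICC)/480)), where 480 = 40 × 12.
- ICC 0.2: sqrt(2 × (0.00500 + 0.00167)) = 0.1155
- ICC 0.5: sqrt(2 × (0.01250 + 0.00104)) = 0.1646

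**The article's own figures.** Detectable effect = (z for alpha + z for power) × SE.

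| | ICC 0.2 | ICC 0.5 |
|---|---|---|
| Stated, labelled two-tailed | 0.30 | 0.41 |
| Two-sided, (1.960 + 0.842) × SE | 0.323 | 0.461 |
| One-sided, (1.645 + 0.842) × SE | 0.287 | 0.409 |

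The stated figures are not reproduced as two-tailed; they sit closer to a one-tailed calculation. They would fit a two-tailed one if covariates explained about 14% and 21% of the variance of the group means, but none is stated. The next step is therefore run with two sets of standard errors: those above, and those implied by taking the stated figures at face value (0.30/2.80 = 0.107 and 0.41/2.80 = 0.146).

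**Chance of a non-significant two-sided test when mobile fidelity is truly worse.** This is approximately Φ(1.96 − deficit/SE).

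| True deficit | Standard errors used | ICC 0.2 | ICC 0.5 |
|---|---|---|---|
| 0.30 SD | derived | 26% | 55% |
| 0.30 SD | implied by the article | 20% | 46% |
| 0.20 SD | derived | 59% | 77% |
| 0.20 SD | implied by the article | 54% | 72% |

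**What a null result leaves open.** With an estimate near zero, the 95% interval extends 1.96 × SE either way: about 0.23 SD at ICC 0.2 and 0.32 SD at ICC 0.5. Both exceed the 0.21 SD limit used for youth outcomes.

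**What a noninferiority test could support.** With a true difference of zero and one-sided alpha 0.05, power = Φ(margin/SE − 1.645), using the derived standard errors.

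| Margin | ICC 0.2 | ICC 0.5 |
|---|---|---|
| 0.21 SD | 57% | 36% |
| 0.30 SD | 83% | 57% |
| 0.41 SD | 97% | 80% |

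The smallest margin with 80% power is about 0.29 SD (ICC 0.2) or 0.41 SD (ICC 0.5). At one-sided 0.025 these become 0.32 and 0.46 SD.

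**The case against.** The strongest reply is that the article never says a non-significant fidelity result will be called comparable. That stands. A reader might infer such a rule, since under the stated test only non-rejection agrees with the hypothesis, but the article states no decision rule. Other tempting readings also go too far:

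- **That fidelity is the primary outcome.** Aim (a) lists feasibility, acceptability, cost and fidelity together, and none is singled out as primary.
- **That the Study aims section itself states a null of no difference.** It states research hypotheses. For youth outcomes its wording is loosely compatible with noninferiority. The contradiction lies between the Quantitative analysis section and the power section for student outcomes.
- **That no fidelity margin exists.** A condensed article may leave the number to the analysis plan. It does not leave the type of test open: both the analysis and the fidelity power section specify no difference, and the detectable effects are given for that test.
- **That the miss rates above are firm, or that school clustering must raise them.** They depend on which standard error is used. The article gives no school-level figure for fidelity, and matching schools into quintets could lower the standard error.
- **That a deficit of 0.20 or 0.30 SD is materially worse fidelity.** Nothing in the article says what loss of fidelity matters.

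None of these points closes the gap between the hypothesis and the test.

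**Conclusion.** The point holds as a mismatch between a stated hypothesis and a stated test, together with an internal contradiction over youth outcomes. The fidelity test as written and powered can show that the two forms of supervision differ; it cannot show that they are comparable. The logic does not depend on any numerical assumption.

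The size is illustrative. A true deficit of 0.30 SD would be missed about 26% to 55% of the time across the article's two ICCs, or about 20% to 46% on the standard errors implied by its own detectable effects. These figures assume two-sided alpha 0.05, equal arms of 40 groups, 12 ratings each and no school-level effects. They show how weak the evidence from a null result could be. They do not show that such a deficit is important or that the team would misreport it.

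**What to change.** 1. In the Quantitative analysis section and the fidelity power section, replace the test of no difference for fidelity with a one-sided noninferiority test. Apply it to a prespecified contrast from the planned growth model; the mean over sessions is one option.
2. State and justify a margin on the checklist's own scale, and fix it before any arm-level fidelity data are seen. By the article's account data collection had not started, so this was still possible at publication.
3. Claim comparable fidelity, as hypothesised in Study aims, only if the confidence limit for mobile minus standard excludes a deficit as large as the margin. Report a result that neither excludes the margin nor shows a significant deficit as inconclusive.
4. Restate the fidelity power on that basis, with alpha, power and any covariate assumption given. With one-sided alpha 0.05 and the assumptions above, the 80 groups give 80% power for margins of about 0.29 SD (ICC 0.2) to 0.41 SD (ICC 0.5).
5. Align the youth-outcome paragraph of the Quantitative analysis section with the noninferiority test in the power section for student outcomes.

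**Cost.** The change needs revised wording, a justified margin and a new power statement, with no added data collection if margins of that size are acceptable. Some results that would have been called not different become inconclusive. A tighter margin would have less than 80% power with the planned groups: applying 0.21 SD to fidelity would need about 75 (ICC 0.2) or 152 (ICC 0.5) groups per arm, against 40 planned.

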### Intervention description

The YRI is a culturally informed, 12-session, transdiagnostic group intervention that integrates core components of cognitive behavioral and interpersonal therapies as well as mindfulness techniques (i.e., psychoeducation, cognitive restructuring, behavioral activation, interpersonal effectiveness, problem-solving). Sessions typically last approximately 90 min each and incorporate both psychoeducation as well as activities and home practice to hone skills learned. The main objectives of the YRI are to improve emotion regulation, adaptive coping, and interpersonal skills (See Table 1). In the current study, the YRI will be delivered once per week during a time identified by schools when teachers and youth are available.

**Table 1 Tab1:** YRI Session Modules

Module	Components
1. Introductions and building group cohesion	• Introduces the format and goals of the intervention • Provides an opportunity to begin building trust, motivation for group participation, and group cohesion • Participants identify personal goals that group participation will help them achieve
2. Psychoeducation on Stress and Emotions	• Psychoeducation on traumatic stress reactions in order to normalize this experience for group participants • Participants learn about emotions, how to identify them and how this skill will help them reach their goals
3. Understanding the link between beliefs, bodies and behaviors	• Participants learn about the link between what you think, how it makes you feel, and how you behave • Participants identify healthy and unhealthy coping behaviors and discuss the impact of coping skills on reaching their goals
4. Taking control of your life	• Introduces concept of emotion-regulation and coping skills as one way of taking charge of your life • Practicing of coping strategies and recognizing things you can change and things you cannot • Processing loss and teaching emotion regulation strategies: behavioral activation and deep belly breathing
5. Relaxation and emotion regulation	• Participants reflect upon what types of behaviors can alter their mood for the better • Review of belly breathing and learn about guided imagery (safe spaces) • Participants identify fun activities that can disrupt negative thinking
6. Dealing with the past, things lost/things gained	• Focus on normative reactions to life disruption and loss related to traumatic experiences and loss • Participants reflect on things lost but also things gained in their lives

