YRI facilitators (teachers) in both study conditions will complete the fidelity and competency checklists after each session and audio record all sessions. Given the potential bias of self-report, supervisors will also code randomly selected 20-minute segments after each session. YRI fidelity checklists include both cross-cutting session items (e.g., encourages participation) to assess competency and session-specific items (e.g., facilitator reviewed deep belly breathing) to assess fidelity to content. Mobile-based supervision will include a designated 30–45 min weekly “supervision chat” using WhatsApp, review of audio taped session segments and fidelity and competency checklist data, as well as options for asynchronous messaging and chats as needed to provide targeted and supportive feedback, share lessons learned, and answer questions. Standard supervision will occur via weekly 30–45 min in-person sessions and include review and discussion of fidelity data. YRI facilitators who receive mobile-based supervision will complete the YRI fidelity and competency checklists as an electronic fillable form embedded in the mHealth app; those who receive standard supervision will complete a manual checklist in Excel uploaded to a secure server (Box).

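### The planned fidelity model estimates fidelity in sessions held, so it could find comparable fidelity even if one arm delivered fewer of the 12 sessions

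*Protocol article*

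**What the plan says.** The intervention is a "culturally informed, 12-session, transdiagnostic group intervention" (Intervention description), planned weekly, with two groups in each intervention school.

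Both sources of fidelity data depend on a session having occurred (YRI training and supervision). Teachers "will complete the fidelity and competency checklists after each session and audio record all sessions", and "supervisors will also code randomly selected 20-minute segments after each session". The checklist has cross-cutting items for competency and "session-specific items (e.g., facilitator reviewed deep belly breathing) to assess fidelity to content". The section on implementation outcomes names these checklists as the fidelity measure: "Fidelity will be assessed using the YRI fidelity checklists completed either via an electronic fillable form in the app" in the mobile arm, or in spreadsheets in the standard arm.

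Study hypothesis (a) includes the statement that "YRI fidelity scores for mobile supervision will be comparable to standard supervision" (Study aims). The test is a comparison of fidelity trajectories by multilevel growth models. On gaps, the Quantitative analysis section says: "Missing time points are addressed by the multilevel approach to growth modeling, and data from all enrolled participants can be analyzed", and it calls this intention to treat. The same paragraph mentions multiple imputation in the HLM software. The power calculation is made "for 80 groups and 12 fidelity ratings".

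The article names no count of sessions delivered as an outcome. Adoption is measured by questionnaire.

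**The concern.** A rating can be absent for two different reasons. If the session was held and the checklist or recording was lost, a fidelity value existed and was not observed. Missing-data methods are meant for that case. If the session was never held, there was no performance to rate, and the model has nothing to recover. What it then describes is how faithful the sessions are when they take place.

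This matters because the hypothesis is one of comparability. Keeping teachers delivering is plausibly part of what supervision does, so a difference in sessions held may be an effect of the supervision mode. An analysis that cannot register such a difference could report comparable fidelity while youth in one arm received less of the programme. Costs are prorated to actual effort, so an arm that held fewer sessions could also look cheaper at the same apparent fidelity.

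The statement that all enrolled participants can be analysed also fails for this outcome where a group never starts, because that group has no rating.

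**Working it through.** **Inputs from the article.** There are 12 planned sessions per group, 20 schools per supervision arm and 2 groups per school. That gives 40 groups per arm, 80 in all, and 40 x 12 = 480 planned ratings per arm. The power section's 80 groups with 12 ratings each (960 ratings) is the full-delivery case. The article gives no delivery rate and no figure for content delivered, so there is no stated result to reproduce on this point.

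**Step 1: which quantity is estimated.** Let q be mean fidelity in sessions held and h the number of sessions held out of 12. A growth model fitted to the available ratings targets q. Content delivered over the planned programme is q x h/12, if the missed content is not made up later. The two agree only when h = 12.

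**Step 2: illustration (q and h are assumptions).** Take q = 85% in both arms, with the standard arm holding 12 of 12. The planned comparison is 85% v 85%, a difference of 0, in every row.

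| Sessions held, mobile arm | Content delivered, mobile arm | Shortfall v 85% |
|---|---|---|
| 11 of 12 | 0.85 x 11/12 = 77.9% | 7.1 points |
| 9 of 12 | 0.85 x 9/12 = 63.75% | 21.25 points |
| 6 of 12 | 0.85 x 6/12 = 42.5% | 42.5 points |

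**Step 3: does a mixed model behave this way?** A simulation used 80 groups and 12 sessions, with 300 runs per scenario and a random-intercept model on the observed ratings. Assumptions: mean 80 on a 0-100 scale, SD 10, equal quality in held sessions, skipping in the mobile arm only.

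| Scenario | Sessions held, mobile | Model difference | Rejection rate | Difference with unheld sessions scored 0 |
|---|---|---|---|---|
| No skipping | 12 | +0.1 | 6% | +0.1 |
| ICC 0.2, 33% skipped | 8.0 | +0.1 | 7% | -26 |
| ICC 0.2, 33% skipped, 20% of groups never start | 6.4 | 0.0 | 7% | -37 |
| ICC 0.2, 50% skipped | 6.0 | -0.1 | 4% | -40 |
| ICC 0.5, 33% skipped, 20% of groups never start | 6.4 | 0.0 | 5% | -37 |

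The last column agrees with direct arithmetic: 80 x 0.33 = 26.4, 80 x (1 - 6.4/12) = 37.3 and 80 x 0.50 = 40. Some fits gave convergence warnings, but the mean estimates stayed near 0. The near-zero model differences follow from the assumption of equal quality in held sessions. The simulation therefore shows that the two quantities can part widely without the model registering it. It does not show that the model is biased for fidelity in sessions held.

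**Step 4: groups that never start.** Such a group contributes 0 of its 12 planned ratings. It has no observation in a likelihood analysis, so its delivery of 0 out of 12 does not enter the fidelity result.

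**The case against.** The strongest reply is that the article does not say an unheld session counts as a missing time point. The sentence fits lost checklists equally well, and the coding of undelivered sessions is detail that an analysis plan may settle. The first part stands: the classification is inferred from reading the rating procedure together with the rule for gaps. The second part stands only partly, because the article does state a rule for gaps in the fidelity trajectories, and that rule makes no distinction.

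Secondly, quality of sessions held is a coherent definition of fidelity, with dose as a separate matter. This stands. It is a reason to label the result and report delivery beside it, not to replace the planned outcome with zero-scored sessions.

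Thirdly, a missed session may be rescheduled or its content covered later. This also stands. An unheld session is not automatically content fidelity of zero.

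Fourthly, under-delivery would not be invisible. Recordings and checklists allow sessions to be counted, session delivery and participants' time are costed, and youth outcomes are compared between arms. That is true of the data, but none of it enters the fidelity comparison as described.

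A reader might also infer that the planned model is biased towards the arm losing more sessions because the remaining groups are the more motivated. Nothing in the article supports that. If fidelity declined before delivery lapsed, a growth model could carry the decline forward. Nor would 120 of 480 ratings (40 groups x 3 sessions) literally be replaced with mobile at 9 of 12: a likelihood model uses the ratings available and need not fill in any.

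**Conclusion.** The point holds as a gap between what the model estimates and what a finding of comparable fidelity would be taken to mean. On a direct reading, the planned analysis gives fidelity conditional on delivery. It can return no difference when one arm delivered fewer sessions, and it takes nothing from a group that never starts.

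The size cannot be stated from the article. In the illustration it runs from about 7 points at 11 of 12 sessions to about 42 points at 6 of 12. This rests on assumed delivery rates, equal quality in sessions held, and no make-up of missed content. If both arms deliver all 12 sessions, or deliver equally at equal quality, the comparison between arms is unaffected. The documents do not show that delivery will differ between arms, or that the model is wrong for fidelity in sessions held.

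**What to change.** In the sections on implementation outcomes and quantitative analysis:

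- Limit the missing-data methods to sessions that were held but not rated, and state that the growth-model result is fidelity in sessions held.
- Report sessions delivered out of 12 by arm for all 80 groups beside it, with 0 for a group that never starts.
- Add an analysis of content delivered over all 12 planned sessions, in which session-specific content never delivered, including in any make-up session, counts as 0.
- Base any conclusion of comparable fidelity on both results.

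The cost is one added derived variable, which will be skewed. A log of sessions held should follow from the checklists, the recordings and the costing of session delivery already planned. Competency on the cross-cutting items remains conditional on delivery. Youth recruitment had not begun when the article was submitted (Trial status), so the definitions could have been fixed before any session was rated.
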